#### Analysis of Secondary Efficacy End Points

Comparison between treatment groups for all secondary end points will be conducted at the final analysis at one-sided alpha of .025.

Time-to-event end points (ie, overall survival, time to symptomatic progression, and time to deterioration in quality of life) will be compared between treatment groups using a log-rank test. Disease control rates and objective response rate will be compared between treatment groups using the continuity-adjusted Newcombe-Wilson test. The FACT-C score will be compared between treatment arms using a mixed linear model with baseline score and the relative time from baseline as covariates.

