## Methods

### Overview of Design

The study is being conducted in accordance with the Declaration of Helsinki. Participating institutions obtained institutional review board approval of the protocol and informed consent form and are responsible for obtaining written informed consent from patients at screening (Multimedia Appendix 1).

EPOCH is an ongoing, open-label, prospective, multicenter, randomized, phase 3 clinical trial. The objective is to evaluate the efficacy and safety of TARE with TheraSphere in patients with mCRC of the liver who have disease progression on first-line chemotherapy with either an oxaliplatin-based regimen or an irinotecan-based regimen and who are eligible for second-line chemotherapy with the alternate regimen. All patients receive chemotherapy; however, in the TARE group, TheraSphere is administered in place of the second cycle of chemotherapy, with chemotherapy subsequently resuming. A maximum of 420 patients are planned to be randomized at up to 100 sites in the United States, Canada, Europe, and Asia. The 2 primary end points are progression-free survival and hepatic progression-free survival. The study objective will be considered achieved if at least one primary end point is statistically significant. All patients are to be followed prospectively from randomization to death until the predefined number of progression-free survival events, to allow the final analysis to be conducted, have occurred.

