### Planned Statistical Analysis

#### Sample Size Estimate

The study is a phase 3 adaptive trial, comprising a group sequential design with 2 interim analyses. The study could be stopped early for efficacy at an interim analysis based on superiority in progression-free survival but not hepatic progression-free survival.

The study is designed to detect a 2.5-month increase in median progression-free survival, from 6 months in the control group to 8.5 months in the TARE group (hazard ratio [HR] 0.71), and a 3.5-month increase in median hepatic progression-free survival time, from 6.5 months in the control group to 10 months in the TARE group (HR 0.65). On the basis of simulations, the power to detect the target difference in either progression-free survival or hepatic progression-free survival is >90%, and the power to detect the target difference in each end point alone is >80%, using log-rank tests.

The analysis of progression-free survival will be based on a group sequential design with 2 interim analyses at 50% and 70% of the required total number of 344 progression-free survival events with a stopping boundary defined by the rho family error spending function with ρ=1.5 [24]. It is estimated that a maximum of 420 patients will need to be recruited over 36 months, with a 1-year additional follow-up period, allowing for 10% of patients lost to follow-up and for whom a date of progression or death is not recorded. Although the forecasted accrual period has been increased to 60 months, this does not increase the number of patients required or affect the statistical power of the study because both the power and the timing of the interim and final analyses are based on the number of progression-free survival events rather than the number of patients. The Hochberg procedure will be used to control type 1 error for the 2 primary end points at the final analysis [25].

A simulation study, assuming that progression-free survival and hepatic progression-free survival have a correlation between 0.3 and 0.8, showed that the power to detect the target difference in either median progression-free survival (ie, HR 0.71) or median hepatic progression-free survival (ie, HR 0.65) is >90%, and the power to detect the target difference in progression-free survival or hepatic progression-free survival alone is >80%. The simulation study also demonstrated control of type 1 error at the nominal one-sided level of 0.025.

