##### Final Analysis of Primary End Points of Progression-Free Survival and Hepatic Progression-Free Survival

The final analysis is planned at 344 progression-free survival events. The Hochberg procedure will be used to control type 1 error for the 2 primary end points [25]. Whichever of progression-free survival or hepatic progression-free survival that has the larger *P* value will be compared between treatment groups using a log-rank test converted to a z-score and compared with the nominal critical value of 2.312 with a corresponding one-sided *P* ≤.0104 required to declare a statistically significant improvement in hazard rate for this end point. To ensure that type 1 error is controlled for both primary end points, this boundary is based on the incremental alpha of .0104 instead of the *P* value scale boundary of .0168, using the rho family error spending function with ρ=1.5.

According to the Hochberg procedure, if the primary end point with the larger *P* value is statistically significant, then the other primary end point is also statistically significant. However, if the primary end point with the larger *P* value is not statistically significant, then the other primary end point will be compared between treatment arms using a log-rank test converted to a z-score and compared with the nominal critical value of 2.562 based on the rho family error spending function, with a corresponding one-sided *P* ≤.0104/2=.0052 required to declare a statistically significant improvement in hazard rate for this end point.

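### The secondary end points are each tested at one-sided .025 with no stated order, alpha split or link to the primary result, so the secondary family carries an error of roughly 6% to 14%

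*Protocol article*

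**What the plan says.** **Primary end points.** Under Sample Size Estimate, multiplicity control is limited to the two primaries: "The Hochberg procedure will be used to control type 1 error for the 2 primary end points at the final analysis". The same section gives the level: "The simulation study also demonstrated control of type 1 error at the nominal one-sided level of 0.025". The section on the final analysis of the primaries adopts a stricter boundary with a stated purpose: "To ensure that type 1 error is controlled for both primary end points". Overview of Design defines trial success by the primaries alone: "The study objective will be considered achieved if at least one primary end point is statistically significant".

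**Secondary end points.** Analysis of Secondary Efficacy End Points opens with one rule: "Comparison between treatment groups for all secondary end points will be conducted at the final analysis at one-sided alpha of .025". It then lists the tests:

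- "Time-to-event end points (ie, overall survival, time to symptomatic progression, and time to deterioration in quality of life) will be compared" (three log-rank tests);
- "Disease control rates and objective response rate will be compared between treatment groups using the continuity-adjusted Newcombe-Wilson test" (two tests);
- "The FACT-C score will be compared between treatment arms using a mixed linear model" (one test).

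That makes six comparisons. Adverse events are also listed as a secondary end point under Efficacy End Points and Definitions, but no test is assigned to them and they are not counted here. The section gives no order, no alpha split and no condition on the primaries.

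**The concern.** A stated alpha is a decision threshold: a result that passes it will be called significant. Here every secondary comparison has the whole of .025 to itself, so the chance that at least one passes by luck grows with the number of tests. As written, the rule also does not depend on the primary result. A reader following the text could report a significant secondary benefit from a trial in which neither primary end point succeeded, with no control over how often that happens by chance. Overall survival is among these end points, so such a statement would carry weight.

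**Working it through.** **Inputs from the article.** One-sided .025 per secondary test; six named comparisons; one-sided .025 for the primary family; rho-family spending with ρ = 1.5 and looks at 172, 241 and 344 events.

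**Assumption.** The correlation among the secondary test statistics is not given. I take 0 to 0.8. The only correlation in the article, 0.3 to 0.8, concerns the two primaries.

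**Step 1: the plan's own figures.** Cumulative spending is 0.025 × t^1.5.

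- t = 0.5: 0.0088
- t = 0.7: 0.0146
- t = 1: 0.0250

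The increments are 0.0088, 0.0058 and 0.0104. The article gives .0057 for the second, a last-digit difference with no bearing here. Solving the boundaries from the joint normal distribution, with correlation √(t_i/t_j), gives z = 2.372, 2.330 and 2.125, that is one-sided P = .0088, .0099 and .0168. These match the article, so .025 is the right benchmark for the primaries. The two-endpoint control rests on the article's own simulation, which was not rerun.

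**Step 2: independent secondary tests.** The chance of at least one false claim when all m nulls are true is 1 − (1 − 0.025)^m.

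- m = 6: 1 − 0.975^6 = 0.141
- m = 5 (the two FACT-C analyses counted once): 1 − 0.975^5 = 0.119

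The Bonferroni ceiling, whatever the dependence, is 6 × 0.025 = 0.150 or 5 × 0.025 = 0.125.

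**Step 3: correlated secondary tests.** With common correlation ρ and c = 1.960, the chance is 1 − ∫ Φ((c − √ρ·x)/√(1 − ρ))^m φ(x) dx.

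| Common correlation | Six tests | Multiple of .025 | Five tests | Multiple of .025 |
|---|---|---|---|---|
| 0 | 0.141 | 5.6 | 0.119 | 4.8 |
| 0.3 | 0.122 | 4.9 | 0.105 | 4.2 |
| 0.5 | 0.104 | 4.1 | 0.092 | 3.7 |
| 0.8 | 0.069 | 2.8 | 0.064 | 2.5 |

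The multiple comes down to about 2 only if all the tests share a correlation near 0.9 (0.054 for six, 0.051 for five). An uneven pattern gives 0.111 for six tests. It assumes 0.6 between overall survival and symptomatic progression, 0.5 between the two response rates, 0.8 between the two FACT-C analyses, and 0.3 elsewhere.

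**Step 4: does a gate alone suffice if the trial stops early?** I simulated one true-null secondary end point, tested at the full .025 at whichever look progression-free survival crosses (2.372, 2.330, 2.312), and took the worst case over the size of the progression-free survival effect. The assumptions are that progression-free survival alone is the gate and that secondary information accrues at the same pace. The error is about 0.027 at a primary-secondary correlation of 0.5 and about 0.032 at 0.8. Both exceed .025, so early stopping needs its own boundary.

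**The case against.** **A hierarchy may sit in an analysis plan that is not shown, and testing each step at .025 would agree with the article's sentence.** This has force: the level alone does not exclude a fixed sequence. But the sentence commits to comparing all secondary end points at that level without condition. A hierarchy elsewhere would have to qualify it. The point rests on the rule as stated.

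**The secondaries may be meant as supportive only, since they cannot make the trial positive.** The second half is correct. The article does not say the first, and a declared alpha suggests otherwise. If that is the intention, one sentence resolves the matter.

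**14.1% overstates the error.** This stands. Objective responders are a subset of the patients with disease control, death counts in both overall survival and quality-of-life deterioration, and two comparisons use the same questionnaire. Independence gives the upper end of the range, not a realistic single value.

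Three stronger readings are tempting, and the article does not support them:

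- *Testing is expressly planned after failed primaries, or secondary results are expressly confirmatory.* Neither is stated in words. The first is what an unconditional sentence permits.
- *Secondaries are judged more leniently than primaries, at .025 against .0104 or .0052.* The .0104 is what is left after alpha is spent at two interim looks, and .0052 is the second Hochberg step. The primary family as a whole also has .025.
- *The open-label design makes the multiplicity worse.* Unblinded assessment is a question of bias, which a gate does not cure. Overall survival is objective, and the two response rates use blinded central review.

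**Conclusion.** The point holds as a defect in the stated secondary testing rule. Followed as written, that rule gives a chance of at least one false secondary claim of about 6% to 7% at an assumed common correlation of 0.8, and 12% to 14% under independence. The lower figure in each pair is for five tests and the higher for six. The primary family is held to 2.5%. The figures assume that all the secondary nulls are true, and they depend on a correlation the article does not supply. The primary analysis and its boundaries are unaffected, and so is the definition of trial success. The change should be made before unblinding.

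**What to change.** Replace the opening sentence of Analysis of Secondary Efficacy End Points with a rule that contains four elements:

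1. **Order.** Formal secondary tests follow a prespecified fixed sequence, for example overall survival first, each at one-sided .025, stopping at the first non-significant result. The order after overall survival is for the sponsor to set.
2. **Gate.** Secondary testing opens only after primary success, under a gate compatible with Hochberg. Requiring both primaries to be significant is valid with ordinary Hochberg. If either primary null is true, the gate opens only through a primary error, which is already controlled. If neither is true, the fixed sequence holds .025 at a single analysis. Opening after one primary would need a truncated Hochberg or similar procedure, so that some alpha remains to pass on.
3. **Early stopping.** If the trial stops at an interim for progression-free survival, the secondaries are tested at a group-sequential boundary and not at the full .025.
4. **Everything else.** P values and confidence intervals outside this scheme are nominal and descriptive. If the sponsor prefers no hierarchy, this label applies to all secondary results and replaces elements 1 to 3.

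The cost is wording, with no new patients or data. Some secondary results lose the label of significance. Under the both-primaries gate, a trial that meets its own success rule on one primary alone could not formally test overall survival, and the plan should say so.

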### Randomization and Stratification

Eligible patients are randomized on day 0 in a 1:1 ratio to either the control group or the TARE group. If the study is not stopped early for efficacy, approximately 210 patients will be randomized to each group. To randomize eligible patients, the study site contacts the central randomization office where randomization will be determined using assignment by a computer-generated randomization scheme. Upon randomization, each patient is assigned an identity code. To ensure that treatment groups are balanced, patients are stratified at randomization based on the extent of liver involvement (unilobar vs bilobar disease), type of first-line chemotherapy (oxaliplatin-based vs irinotecan-based), and KRAS status (wild type vs mutant). Additional factors permitting covariate analysis are captured at randomization but are not stratification criteria. These factors have been defined based on the planned covariate analyses. Patients randomized to either the control or the TARE group who are unable to receive their planned study treatment continue to be followed under their assigned study group for the purpose of the intent-to-treat analysis.

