## Discussion

### Overview

First-line chemotherapy regimens for unresectable mCRC are well established [10]. Second-line therapy using the combination of chemotherapy and targeted therapies has demonstrated efﬁcacy with improved overall survival, progression-free survival, and overall response rate in comparison with chemotherapy alone [26,27]. However, the choice of the optimal treatment strategy remains challenging and is mostly driven by the type of and response to the first-line treatment administered, the type of retrovirus-associated DNA sequence mutation (KRAS, NRAS, and HRAS), microsatellite stability, tumor burden, patient performance status, and comorbidities.

The EPOCH study was designed to account for known prognostic and predictive factors [10]. Patients in the EPOCH study are stratified at randomization according to key factors that could influence the primary or secondary study end points: (1) tumor load (unilobar vs bilobar), (2) KRAS status (wild type vs mutant), and (3) prior first-line chemotherapy (oxaliplatin-based or irinotecan-based) to ensure balance between groups.

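### The response and disease control comparisons use a valid but mildly conservative test that, as worded, leaves out the randomization factors; a stratified uncorrected test would recover a few points of power

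*Protocol article*

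**What the plan says.** The Protocol article, Analysis of Secondary Efficacy End Points, sets the level: "Comparison between treatment groups for all secondary end points will be conducted at the final analysis at one-sided alpha of .025". For objective response rate and disease control rate it names the method: the two groups are "compared between treatment groups using the continuity-adjusted Newcombe-Wilson test". It mentions no strata there.

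Under Randomization and Stratification, patients are "randomized on day 0 in a 1:1 ratio" and, if the trial runs to the end, "approximately 210 patients will be randomized to each group". The same section says that "patients are stratified at randomization based on the extent of liver involvement (unilobar vs bilobar disease), type of first-line chemotherapy" and KRAS status, which makes 2 × 2 × 2 = 8 cells. The Discussion (Overview) gives the reason for choosing these three: they are "key factors that could influence the primary or secondary study end points". Response and disease control are secondary end points.

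Poolability and Other Analyses plans logistic regression of both binary end points along the lines of the Cox models. Each baseline factor, including the three stratification factors, is fitted in turn with randomized group. Multivariable models with site or region then follow, keeping the factors that reach one-sided P<.075.

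**The concern.** Two features of the named comparison cost power.

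- **The method.** Newcombe-Wilson is a confidence interval for a difference between two proportions. Used as a test, it rejects when the interval lies above zero. The continuity adjustment widens the interval, so the test rejects less often than its nominal .025 when there is no effect, and less often when there is one.
- **The strata.** In its standard form the method compares two pooled samples and has no stratum term. The article says the three factors may influence secondary end points, yet the comparison as worded does not use them. Where a factor predicts response, that gives away some precision.

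What is at stake is a modest amount of power for two secondary end points. Enrollment is complete, so the choice of analysis is one of the few ways left to improve it.

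**Working it through.** **No figure to reproduce.** The article states no expected rate, target difference or power for either end point. The check therefore covers a range of assumed rates.

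**Inputs from the article.** 210 per arm and 1:1 allocation (Randomization and Stratification); one-sided .025 and the continuity-adjusted Newcombe-Wilson method (Analysis of Secondary Efficacy End Points); three binary stratification factors.

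**Step 1: the test as a rule.** Let p1 and p0 be the observed proportions in the TARE and control groups. Let l1 be the lower continuity-corrected Wilson 95% limit for p1, and u0 the upper one for p0. The test rejects when

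p1 − p0 − √[(p1 − l1)² + (u0 − p0)²] > 0.

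The comparator is the uncorrected score (Pearson) test, which rejects when (p1 − p0) / √[p(1 − p)(2/210)] ≥ 1.96, with p the pooled proportion.

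**Step 2: exact size.** Add up the binomial probabilities of all outcome pairs (x1, x0) that reject, with the same true rate in both arms.

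| True rate, both arms | Planned test | Score test |
|---|---|---|
| 5% | .0148 | .0241 |
| 10% | .0182 | .0245 |
| 20% | .0199 | .0250 |
| 30% | .0210 | .0251 |
| 50% | .0227 | .0230 |

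The table is symmetric about 50%, so a high disease control rate fares the same way: .0199 at 80% and .0182 at 90%. The uncorrected Newcombe-Wilson version has size .0232 to .0251 over 5% to 90%. The shortfall therefore comes from the continuity adjustment, which is not needed at this sample size.

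**Step 3: exact power (rates assumed).**

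| Control vs TARE | Planned test | Score test | Difference (points) |
|---|---|---|---|
| 10% vs 20% | 79.8% | 82.7% | 2.8 |
| 15% vs 25% | 69.9% | 73.2% | 3.3 |
| 20% vs 30% | 63.1% | 66.1% | 3.0 |
| 20% vs 32% | 78.2% | 80.5% | 2.3 |
| 20% vs 35% | 92.5% | 93.5% | 1.0 |
| 70% vs 82% | 80.4% | 82.6% | 2.2 |

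Differences are taken before rounding. With 189 per arm (210 less the 10% loss to follow-up in the article's sample-size section), planned size is .0141 to .0224 and the loss is at most about 3.5 points.

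**Step 4: stratification.** 8,000 simulated trials of 420 patients per scenario, 8 strata, stratified randomization. Assumed: factor prevalences 60%, 30% and 45%, block size 4, treatment log-odds ratio 0.65.

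| Assumed odds ratio per factor | Planned | Unstratified score | Stratified Cochran-Mantel-Haenszel | Gain from strata | Total gain |
|---|---|---|---|---|---|
| 1.0 | 80.4% | 82.7% | 82.5% | about 0 | 2.1 |
| 1.5 | 78.7% | 81.0% | 81.3% | 0.4 | 2.7 |
| 2.0 | 77.9% | 80.1% | 81.6% | 1.5 | 3.7 |

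Each simulated power has a standard error of about √(.8 × .2 / 8000) = 0.45 points. With no treatment effect, rejection rates were .017 to .020 for the planned test, .021 to .026 for the unstratified score test and .023 to .027 for the stratified test. Leaving out the strata does not inflate type I error. In these scenarios most of the total gain comes from dropping the continuity adjustment.

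**The case against.** The strongest reply is that nothing here is an error. The article names a valid test in advance, type I error stays below .025, and no stated power or rate is missed because none is stated for these end points. That stands, and it is why this is an efficiency suggestion only.

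Second, the absence of strata is read from silence in a condensed article. The full analysis plan is not shown and may specify a stratified version. The primary log-rank tests are equally silent, so the omission is not peculiar to response and disease control. This also stands for the stratification part. It does not touch the continuity adjustment, which the article states outright.

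Third, the logistic models do bring in each factor. A reader might infer that the plan as a whole disregards its stratification factors; the section on poolability and other analyses shows otherwise. However, those models take the factors one at a time, and the multivariable versions keep only those that pass a P-value screen. None is the comparison at one-sided .025, so they soften the point without removing it.

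A reader might also infer a large loss from ignoring strongly prognostic strata. With eight equal strata, a 20% base rate and a treatment log-odds ratio of 0.68, factor effects of ±0.6 on the log-odds scale give 74.5% power as planned against 82.0% stratified. That requires an odds ratio of about e^1.2 = 3.3 for each of three factors, which nothing in the article supports. At ±0.3 per factor the figures are 82.2% as planned, 84.2% unstratified without the correction and 85.4% stratified: 2.0 points from the correction and 1.2 from the strata.

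Finally, moving to a less conservative test late in an open-label trial may look opportunistic. That is a fair caution about timing and documentation.

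**Conclusion.** The point holds as a low-priority improvement. The planned comparison of response and disease control is valid and mildly conservative: one-sided size about .015 to .023 at 210 per arm for assumed rates of 5% to 50%, and about 1 to 3 points of power lost against the uncorrected score test. Stratifying adds about 0 to 1.5 points for weakly to moderately prognostic factors, so both changes together are worth roughly 2 to 4 points. Response rates, stratum prevalences, prognostic strength and block size are all assumed. The documents do not support a claim of inflated error, of an internal contradiction, or of a plan that never uses the stratification factors.

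**What to change.** Before the final unblinded analysis, specify the comparison of objective response rate and disease control rate as a Cochran-Mantel-Haenszel test stratified by lobar extent, first-line regimen and KRAS status, without continuity correction, at the same one-sided .025. Report the stratum-weighted risk difference with its 95% CI. Keep the continuity-adjusted Newcombe-Wilson interval as a descriptive supplement. If the full analysis plan already does this, only the article's description differs and nothing more is needed.

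The cost is wording: the three factors are already recorded at randomization. Two small additions are required. One is a pre-stated rule for pooling sparse cells among the eight strata. The other is a dated record that the change was made before unblinding and without knowledge of response by arm, because enrollment is complete and the monitoring committee has already reviewed a first interim analysis.
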